### Exit criteria

Patients or their authorized representative require withdrawal from the study;Do not achieve DAS28-CRP < 3.2 by the end of 12 weeks in the induction treatment;Relapse during the randomized phase;Because of AE or SAE, the responsible physician considers that the patient is not suitable to continue the trial;Because of protocol violation (PV), the responsible physician considers that the patient is not suitable to continue the trial;Become pregnant.

Participants will be advised verbally and in writing that they will be free to withdraw at any stage upon request.

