## Methods/design

### Study design

This will be a two-stage study. The first stage will serve as an induction treatment with TNFi plus MTX for no more than 12 weeks. Patients who have achieved CR or LDA [defined as disease activity score 28 (DAS28)-CRP ≤ 3.2] in 12 weeks will enter the second stage at the time of CR/LDA achieved. The second stage will be a multiple-center, randomized, outcome assessment blinded, parallel controlled clinical trial. All eligible participants will be randomly allocated to three arms at a ratio of 1:1:1 to receive different treatment strategies for 60 weeks or until relapse.

This study will be expected to be conducted from October 2015 to September 2022. The first patient was recruited on Oct 8, 2015 and the last patient is planned to be recruited by Sep 30, 2021. The study flow-chart is shown in Fig. 1.

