### Concomitant medications

#### Concomitant medication not permitted

Glucocorticoids and other DMARDs, including leflunomide, azathioprine, tripterygium, cyclosporine, and other biological agents.

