### Follow up schedule and data collection

A total of at most 14 visits will be scheduled. Data to be collected at each visit are summarized in Table 1.

**Table 1 Tab1:** Follow up schedule and data to be collected

Study period	Induction treatment stage		Randomized stage										Early exit
Visit	S1	S2-4	V0	V1	V2	V3	V4	V5	V6	V7	V8	V9	
	Wk0	Wk 4\8\12	Wk0	Wk4	Wk8	Wk12	Wk20	Wk28	Wk36	Wk44	Wk52	Wk60	
ICF	√												
Demographic data	√												
Past history and medication history collection	√												
Physical examination	√	√ √	√	√	√	√	√	√	√	√	√	√	√
Urine βHCG (if applicable)	√												
BCC, renal function, liver function, ESR,CRP,RF	√	√	√	√	√	√	√	√	√	√	√	√	√
Assessment committee examination	√	√ √	√	√	√	√	√	√	√	√	√	√	√
IC/EC judgement	√												
Randomization		√											
Hand X-ray-ran	√		√									√	√
Ultrasound of double hands	√		√									√	√
Anti-CCP antibody	√											√	√
Cost of exam and treatment	√		√	√	√	√	√	√	√	√	√	√	√
HAQ-DI/EQ-5D	√		√			√						√	√
Study Medication record	√	√	√	√	√	√	√	√	√	√	√	√	√
Concomitant medication record	√	√ √	√	√	√	√	√	√	√	√	√	√	√
AE record	√	√ √	√	√	√	√	√	√	√	√	√	√	√

*ICF* informed consent form, *BCC* blood cells count, *ESR* erythrocyte sedimentation rate, *CRP* c reactive protein, *RF* rheumatoid factor, *IC/EC* inclusion criteria/exclusion criteria, *Anti-CCP antibody* anti-cyclocitrulline polypeptide antibody, *HAQ-DI/EQ-5D* Health Assessment Questionnaire Disability Index/ Euro Qol five dimensions questionnaire, *AE* adverse event

Patients will be requested to return the residual drugs to obtain new drugs at each visit. Laboratory tests must be performed in the eligible study centers. These strategies were designed to improve adherence of subjects.

Subjects who relapse or cannot tolerant adverse effects before the end of the trial should exit the trial and receive empirical treatment, including but not limited to, other biological agents, or csDMARDs combination therapy. All patients who exit early will be kept in following up for the safety and cost-effectiveness analysis.

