### Study outcomes

The primary outcome will be disease relapse, which is defined as DAS28-CRP increases by at least 0.6 compared with that at randomization and is greater than 3.2 simultaneously.

The secondary outcomes will include the following: the incremental cost per reducing 1 case of relapse; change of disease activity score from baseline, assessed by DAS28-CRP, DAS28-ESR, CDAI and SDAI, at 60 weeks after randomization; duration of maintaining CR or LDA after randomization; change of hands X ray modified Sharp score at 60 weeks after randomization; ultrasound remission of hands at 60 weeks after randomization; Health Assessment Questionnaire Disability Index (HAQ-DI) and health related quality of life [the five-levele EuroQol-5D-5L (EQ-5D-5L) and short form-6D (SF-6D)] at 60 weeks after randomization; adverse events and complications; and patient reported outcomes (PRO) including rash, nausea, vomiting, diarrhea, abdominal pain and fever.

All outcomes will be measured after 60 weeks.

Responsible physicians will monitor and record any adverse events (AEs) during the whole trial. Expected AEs will include: allergy; ALT and AST elevation; hemocytopenia; infection; digestive tract symptom including nausea and vomiting; and hemorrhage of digestive tract defined by fecal occult blood positive, etc. In case of AEs, symptomatic treatment or reduction of drug dosage or even discontinuation of drugs will be carried out when necessary. If the drugs is tapered or discontinued, a serious AE will be considered and the patient should exit the study. Physicians will assess the association between intervention and AEs on a 6-point scale (1 = definitely related; 2 = probably related; 3 = possibly related; 4 = probably not related; 5 = definitely not related; 6 = unknown). All AEs will be categorized into three levels using the Spilker classification [(1) mild = not need additional intervention, nor significantly inhibit normal life function of the participant; (2) moderate = significantly inhibit the normal life function of the participant, and may need additional intervention, recovering afterwards; and (3) severe = require intensive intervention, and leave sequelae).

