Serious adverse event (SAE) is defined as any of the following conditions: (1) threat to life; (2) lead to hospitalization or extend hospital stay; (3) lead to permanent or notable disability or functional disorder; and (4) lead to taper or discontinue the study drugs. In case of SAE or scheme violation during study duration, the relevant Institutional Review Board (IRB) and the leading study site (Peking University First Hospital) will be informed and will decide whether the trial will continue or not. Patients will be followed even if protocol has been breached for any reason. The SAE will be recorded as safety outcome.

An independent assessment committee will be set up for outcomes evaluation. The assessment committee will be blinded to the treatments. However, in case of “SAE”, unblinding will be permitted.

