Once approved, the study protocol may not be changed at will. In case the protocol must be verified, the principle investigator, the responsible person of clinical research center and the principle investigators at all sites should discuss and agree on the updates. When an agreement is achieved, protocol revision note should be formulated and signed, and the revised protocol should be submitted to the IRB for approval before implementation.

To guarantee the quality of the study, all the staffs should receive a standard training before start of the trial, including good clinical practice (GCP), subject protection and ethical requirements, study protocol, standard operation procedures, CRF filling instructions, and standard assessment method of disease activity. The project training will run throughout the whole process of the study. The investigators and the study coordinators can add training contents according to actual need.

Treatment that changes during the whole study period will be recorded. To guarantee the correct injection method, each injection of TNFi will be performed in the study centers by medical staffs rather than at home by patients themselves.

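### Relapse rests on DAS28-CRP readings alone, so a flare treated with a prohibited drug between readings can be scored as relapse-free

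*Protocol article*

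**What the plan says.** **Outcome.** Under Study outcomes in the protocol article, relapse means that "DAS28-CRP increases by at least 0.6 compared with that at randomization and is greater than 3.2 simultaneously". The definition has no treatment-failure component.

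**Prohibited treatment.** The section on concomitant medication not permitted lists "Glucocorticoids and other DMARDs, including leflunomide, azathioprine, tripterygium, cyclosporine, and other biological agents". It does not say that taking one counts as relapse or ends participation. Dose titration of MTX is described, under Interventions, only for the induction stage. For the rest, the Discussion says "Treatment that changes during the whole study period will be recorded".

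**Exit.** Relapse in the randomized phase is an exit criterion without further condition. A protocol violation leads to exit only on a judgement: "Because of protocol violation (PV), the responsible physician considers that the patient is not suitable to continue the trial". Study outcomes adds: "Patients will be followed even if protocol has been breached for any reason".

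**Who is blinded.** The randomized stage is a "randomized, outcome assessment blinded, parallel controlled clinical trial", and "The assessment committee will be blinded to the treatments". The treating physician is not named as blinded.

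**Timing and analysis.** Table 1 schedules committee assessment at weeks 0, 4, 8 and 12, then every 8 weeks to week 60, and at early exit. Study and concomitant medication are recorded at each of these visits. Statistical analysis compares A with C by intention to treat, with per-protocol analyses as sensitivity analyses.

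**The concern.** TNFi is withdrawn in groups A and C at week 12, which is also when the interval between readings lengthens to 8 weeks. A flare that starts and is treated inside such an interval may be controlled by the next reading. If the patient stays in and no later reading meets the limit, the definition returns no relapse, and it does so because of the added treatment. This is not a missing-data problem: the outcome is observed but misclassified.

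At stake is the primary contrast between A and C. The duration of maintained remission or low disease activity, a secondary outcome, depends on the same readings. The physician who decides whether the patient stays in very probably knows the arm: the regimens differ visibly, and centre staff give every TNFi injection. The frequency of such treatment may therefore differ between arms.

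**Working it through.** **1. The protocol's own figure.** Inputs from Sample size estimation: relapse 50% in A and 74% in C, two-sided 0.05, power 0.80. The unpooled two-proportion formula gives

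n = (1.960 + 0.842)² × [0.50 × 0.50 + 0.74 × 0.26] / 0.24² = 7.849 × 0.4424 / 0.0576 = 60.28, rounded up to 61.

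This reproduces the stated 61 per group. With 20% dropout, 61 / 0.8 = 76.25, so 77; the planned 80 covers it. The sample size is not at fault.

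**2. Model for masking.** Let fA and fC be the shares of true relapses that are treated and never meet the limit afterwards. The documents give neither share, so all values below are assumptions. The observed rate is the true rate × (1 − f), so

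observed difference (C − A) = 0.74(1 − fC) − 0.50(1 − fA) = 0.24 − (0.74 fC − 0.50 fA).

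**3. Direction.** The difference shrinks when 0.74 fC > 0.50 fA, that is, when fA < 1.48 fC. Equal shares always shrink it, because C has more relapses to mask. It grows only if the share in A exceeds about one and a half times the share in C.

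**4. Size.** Each power cell gives the pooled-variance value, then the unpooled value (the formula that reproduces 61).

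| Masked A / C | Observed A v C | Difference | Power, 61 per arm | Power, 80 per arm |
|---|---|---|---|---|
| 0 / 0 | 50% v 74% | 24.0 points | 0.79, 0.80 | 0.89, 0.90 |
| 10% / 10% | 45% v 66.6% | 21.6 points | 0.67, 0.69 | 0.79, 0.80 |
| 5% / 10% | 47.5% v 66.6% | 19.1 points | 0.57, 0.58 | 0.69, 0.70 |
| 10% / 0 | 45% v 74% | 29.0 points | 0.91, 0.93 | 0.97, 0.97 |

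Example, second row, unpooled at 61: standard error = √[(0.45 × 0.55 + 0.666 × 0.334) / 61] = 0.0878; 0.216 / 0.0878 = 2.461; power = Φ(2.461 − 1.960) = 0.69.

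The column for 80 assumes that all randomized patients contribute an outcome; the column for 61 is the planning number after dropout.

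**The case against.** **The pathway is narrow.** This is correct. A flare that meets the limit at a visit counts as relapse, and treatment comes afterwards: "Subjects who relapse or cannot tolerant adverse effects before the end of the trial should exit the trial and receive empirical treatment". Masking needs a flare between readings, a prohibited drug, a decision to keep the patient in, and no qualifying reading through week 60. A short course that hides one reading leaves later blinded readings able to catch the event. A reader might infer that any treated flare counts as no relapse; the documents do not support that.

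**No section states this scoring, and an analysis plan not shown may settle it.** The first part is true: the scoring follows from the literal definition. The second part is weaker. The primary outcome is fixed in the protocol and written out in full, so an analysis plan that scored treatment as relapse would be changing that definition.

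**Safeguards exist.** A monitor independent of the investigators checks violations and study medication, centre staff inject TNFi, and residual drug is returned. These make an unnoticed restart of trial TNFi unlikely. They do not say how a recorded violation is scored. The per-protocol analysis would probably drop such patients rather than count them as failures.

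**The cost-effectiveness result.** A reader might infer that its proportion without relapse carries the same error. The base case uses the Per-Protocol Set, which would ordinarily exclude users of prohibited drugs, so that inference is not supported as it stands.

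**The remedy has a bias of its own.** This stands. If physicians who know the arm treat patients on MTX alone more readily, counting treatment starts as relapse creates more events in C and favours A. The extended definition should therefore not replace the blinded reading.

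**Conclusion.** The point holds in limited form. As written, the definition scores some treated flares as relapse-free under intention to treat, and nothing in the article prevents it. The sections set out what is prohibited, who is followed and who may leave, but not how the outcome is scored after a prohibited drug.

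It would be tempting to call the primary contrast biased towards no difference. That is true for equal masked shares and for more masking in C, but a share in A above about 1.48 times that in C reverses it. The size cannot be established from the documents. The illustrations (21.6 or 19.1 points instead of 24) rest on assumed shares and treat each masked relapse as masked until week 60, so for those shares of treated flares they are upper bounds if later readings recover some events. That the physician knows the arm is an inference from the regimens, and the article describes no rescue provision for patients who stay in.

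**What to change.** Before database lock, prespecify a second relapse definition. It would count the DAS28-CRP criterion or the start, for RA activity, of a prohibited glucocorticoid, DMARD or biologic before week 60, including a TNFi restart in A or C, dated at that start. Report it alongside the blinded DAS28-only definition, and require the A versus C conclusion to hold under both. Where possible, obtain the blinded committee assessment that Table 1 already provides for early exit before such treatment starts.

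The sponsor must also reconcile Interventions, the list of prohibited medication, Study outcomes, Exit criteria and the Discussion on what follows prohibited treatment or a change of MTX dose in the randomized stage. Until that is done, an MTX increase should not be declared a relapse. No clinical rule is proposed here.

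**Cost.** An amendment to the outcome definition and programming from medication records already kept at every randomized-stage visit. The article reports 123 patients randomized of 240 planned and the trial ongoing, so the rule can still be set in advance. **Downside to state.** Some starts would not have met the DAS28 limit, and decisions by physicians who know the arm can create events, possibly more in C. The DAS28-only analysis is the check on both.

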### Data management and quality control

The Data Management Department of PUCRI (PUCRI-DM) will be responsible for data management, including developing an electronic CRF and data capture system, drafting the data management plan, the data verification plan, plans for promoting participant retention and completing follow-up, and plans for data entry, coding, security and storage. Data management plan will describe details of the whole process of data management, schedule, and responsibilities of every staff. The system will support electronic signature, access control, data query and trace management. The database will be locked before transferring to the statistician for data analyses.

A special training session on the study protocol and CRF will be provided before the initiation of the study at each study site. The on-site monitoring will be conducted by the clinical researchers from the PUCRI at the beginning, in the middle and at the end of the study to ensure the study protocol is not violated.

The PUCRI will assign a project specialist to be responsible for the data monitoring. The monitor will confirm the implementation of the project, the compliance of data record and relevant regulations. The content of monitoring will include signing of ICF, incidence of SAE and PV, as well as management of study medications. After monitoring, a report will be generated and submitted to the project managers. The monitor will be independent of the investigators and sponsor.

Auditing of the trial will be conducted after complement of the study by the finance department which is independent of the investigators and the sponsor.

#### Sample size estimation

According to the study purposes, a superiority design was considered appropriate. Our hypothesis is that the relapse rate in group A (triple therapy group) will be lower than that in group C (MTX monotherapy group) in 60 weeks after randomization.

Sample size was calculated by PASS 11.0. It was reported that for patients with established RA achieving CR or LDA by TNFi combined with MTX, 24% to 85% suffered from disease relapse after discontinuation of TNFi [4–7]. When combined csDMARDs preserved after TNFi removed, the rate of relapse was 51.2–58% [4, 7]. We assume that adding HCQ + SSZ 3 months before the removal of TNFi may somehow decrease the relapse. Accordingly, we expect the relapse rate as 50% in patients in triple therapy group, and 74% in MTX monotherapy group. With a power of 0.8 and a significance level of 0.05 (two-sides), using a 1:1:1 treatment allocation of enrollment, to detect the difference of relapse rate between the two groups, the required sample size is 61 for each group. Given the estimated dropout rate of 20%, we intend to recruit a total of 240 subjects (80 for each group).

We assume that the relapse rate may be similar between group A and group B (TNFi maintenance therapy group), and the cost-effectiveness may be better in group A than in group B. The relapse rate and cost-effective comparison between group A and group B will be exploratory and there was no relevant research hypothesis, so the sample size was not calculated by it.

#### Statistical analysis

All statistical analyses will be performed using SAS 9.2.

The compatibility of baseline data among three groups will be checked. Student’s t-test or Wilcoxon rank sum test will be used for quantitative variables. Chi-square test or Fisher’s exact test will be used for categorical variables. The Cochran–Mantel– Haenszel test or the Wilcoxon rank sum test will be used for ordinal variables.

To compare the relapse rate between triple therapy group and MTX monotherapy group, the intention-to-treat principle will be followed. Considering the influence of central effect, the collected data will be estimated by mantel Haenszel method with stratification by study centers. Kaplan–Meier curves will be used to show the differences of relapse rate among three groups. The disease activity changes and other continuous secondary outcomes (Sharp score, ultrasonic Doppler score and HAQ-DI score) will be compared between the study groups using the covariance analysis model. Per protocol analyses will also be conducted as sensitivity analyses.

Pharmaceutical economics analysis will be performed. Base case analysis and sensitivity analysis will be performed by decision tree model based on Per-Protocol Set (Fig. 2). A series of one-way deterministic sensitivity analysis will be conducted. For the cost-effectiveness analysis, the proportion of not relapse will be taken as effectiveness. The direct cost (medical expenses), indirect cost (productivity lost), total cost (the total of direct and indirect cost), and average cost/effectiveness ratio of each treatment strategy will be calculated. Direct cost will include the cost of experimental drugs, laboratory and radiology examinations, AE/SAE treatment, traffic expenses and accommodation fees directly related with follow-up visit. Indirect cost will include loss of income due to the patients’ and their family’s inability to work due to RA. The incremental cost effectiveness ratio (ICER) of group A and group B against group C will be calculated. Cost-utility analysis will be performed by using EQ-5D-5L and SF-6D as utility index. The costs and average cost/utility ratio of each treatment strategy will be calculated. The incremental cost utility ratio [the cost of increase 1 quality adjusted life year (QALY)] of group A and group B against group C will be calculated. The treatment strategy will be considered to have cost-utility if the incremental cost utility ratio is below 3 times of China’s per capita GDP in the past year (¥100,000).

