
Participants will be recruited into this study from seven participating research centers. As soon as the patients achieve DAS28-CRP ≤ 3.2 during the induction phase, they will be further recruited into the second stage of randomized phase. Patients who do not achieve clinical remission or LDA by the end of 12 weeks of the induction phase will exit the study and receive empirical treatment.

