### Randomization

The blocked randomization, stratified by study center and gender of patients, will be performed centrally when CR or LDA is achieved (V0, week 0). The staffs responsible for randomization will obtain the group allocation code from the Peking University Clinical Research Institute (PUCRI) through an Interactive Web Response System (IWRS).

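### The relapse rule ties the required DAS28-CRP rise to the value at randomisation, but the primary A vs C analysis adjusts for centre only, leaving out that value and gender.

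*Protocol article*

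**What the plan says.** All references are to the protocol article.

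- **Entry.** Under Study design, responders to induction "will enter the second stage at the time of CR/LDA achieved". Eligibility criteria says the same: "As soon as the patients achieve DAS28-CRP ≤ 3.2 during the induction phase" they move to the randomised stage. No lower limit is set. Table 1 places the qualifying visits at weeks 4, 8 and 12.
- **Primary outcome.** Study outcomes defines relapse as "DAS28-CRP increases by at least 0.6 compared with that at randomization and is greater than 3.2 simultaneously".
- **Randomisation.** Allocation is "stratified by study center and gender of patients". Disease activity is not a stratum.
- **Primary analysis.** For the intention-to-treat comparison of group A with group C, Statistical analysis states that "the collected data will be estimated by mantel Haenszel method with stratification by study centers".
- **Other analyses.** Disease activity change and the other continuous secondary outcomes "will be compared between the study groups using the covariance analysis model". No covariate-adjusted analysis of relapse is named. The only sensitivity analysis named for efficacy is per protocol.
- **Planning values.** Under Sample size estimation, "we expect the relapse rate as 50% in patients in triple therapy group, and 74% in MTX monotherapy group", with 61 required per group and 80 to be recruited.

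**The concern.** The value at randomisation appears in both limbs of the relapse rule. It is the reference for the 0.6 rise, and it sets how far the patient is from 3.2. Two patients with the same worsening can therefore be classified differently because one entered in deeper response.

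A variable with that role is a natural covariate, and it is known for every randomised patient because it triggers randomisation. The design does not balance it and the primary analysis does not use it. If it predicts relapse well, the A vs C interval is wider than the data require, and a chance difference in depth of response moves the estimate. If an imbalance showed up in the planned baseline comparison, an adjustment chosen then would be post hoc, in a trial where only outcome assessment is blinded.

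Gender is a smaller instance of the same gap: it is used to randomise but not to analyse.

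**Working it through.** **1. The plan's own figure.** Inputs from Sample size estimation: 50% and 74% relapse, power 0.80, two-sided 0.05. The unpooled two-proportion formula gives

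n = (1.960 + 0.842)² × (0.50×0.50 + 0.74×0.26) / 0.24² = 60.3, rounded up to 61 per group.

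The stated 61 is reproduced. By the pooled test, 61 per group has 78.7% power and 64 has 80.6%, so there is little slack at 61.

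**2. Required rise.** From the relapse definition, required rise = max(0.6, just over 3.2 − V0).

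| V0 DAS28-CRP | Rise needed |
|---|---|
| 1.2 | over 2.0 |
| 1.5 | over 1.7 |
| 2.0 | over 1.2 |
| 2.4 | over 0.8 |
| 2.6 to 3.2 | 0.6 (marginally more at exactly 2.6) |

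The rule is flat from 2.6 to 3.2 and becomes harder to meet below 2.6.

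**3. How much of relapse V0 explains.** The document gives neither the V0 distribution nor the spread of later change, so both are assumed. Both set-ups use a settled DAS28-CRP on treatment with mean 2.8 and SD 0.8, reading SD 0.3 to 0.5, SD of later change 0.6 to 1.0, six post-withdrawal visits, and overall relapse set to 50% (A) and 74% (C). The precision factor is √(1 − R²).

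| | V0 as a steady-state draw, kept if ≤ 3.2 | V0 as the first reading ≤ 3.2 on a falling curve |
|---|---|---|
| Share with V0 < 2.6 | about 60% | 25–35% |
| Relapse variance explained | about 6–19% | about 0.3–2% |
| Interval narrowing | √(1−0.06) = 0.97 to √(1−0.19) = 0.90, so 3–10% | √(1−0.02) = 0.99, so 1% or less |
| Relapse in A, V0 < 2.6 vs 2.6–3.2 | 40–45% vs 59–65% | 0 to 7 points apart |
| Relapse in C, V0 < 2.6 vs 2.6–3.2 | 65–69% vs 82–87% | 0 to 7 points apart |

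The second set-up adds a starting DAS28-CRP with mean 4.8 and SD 0.9, with 50%, 75% and 100% of the fall reached by weeks 4, 8 and 12. It is closer to the entry rule as written. Within it, explained variance is under 1% if improvement continues after V0 and reaches 2% if it stops there.

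**4. Power.** In a separate simulation V0 is uniform from a lower limit L to 3.2 and the largest later change is normal with SD s. There are 61 per arm and 4,000 runs per scenario. The unadjusted test is compared with Mantel-Haenszel on V0 tertiles.

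| L | s | Power, unadjusted → adjusted |
|---|---|---|
| 1.2 | 0.6 | 78% → 88% |
| 1.2 | 1.0 | 79% → 83% |
| 1.6 | 0.6 | 79% → 84% |
| 1.6 | 1.0 | 79% → 81% |
| 2.0 | 0.6 | 80% → 81% |
| 2.0 | 1.0 | 79% → 78% |
| 2.6 | 0.6–1.5 | about 79% → 78% |

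The variance of the unadjusted risk difference is 0.98 to 1.28 times that of the adjusted one. The mean difference is about −0.24 either way.

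**5. Chance imbalance.** If half the patients have V0 < 2.6 (an assumption), the SD of the between-arm difference in that share is √(2×0.25/80) = 0.079. A gap of 10 points or more then occurs in about 21% of trials with 80 per arm, and 27% with 61. In the steady-state set-up the strata differ by roughly 13 points (82 − 69) to 25 points (65 − 40), so a 0.10 imbalance moves A − C by about 1.3 to 2.5 points. In the first-crossing set-up it moves it by less than 1 point.

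**The case against.** The strongest reply is that nothing here is wrong. A centre-stratified Mantel-Haenszel comparison of a binary outcome is a valid randomised analysis, and its standard error already allows for chance imbalance. Even a 2.5-point shift is small beside a 24-point planned effect and a 95% half-width of about 17 points at 61 per arm (1.96 × √(0.4424/61)) or 15 at 80. The planned check of baseline data would show an imbalance, and an analysis plan not shown could add covariates. Entry at the first qualifying reading also tends to bunch V0 near 3.2, where the rule is flat and adjustment gains nothing.

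Most of this stands, and it limits the point to efficiency. It does not remove it. The article is not silent: it names the primary method and its one stratifier. A better use of a value already in hand changes that named method at no cost in data.

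A reader might infer more than the document supports:

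- **That the comparison is biased or its type I error inflated.** Randomisation protects it, and the simulated mean difference is unchanged by adjustment.
- **That V0 is the strongest predictor of relapse.** This cannot be known without its distribution. Under the entry rule as written it may explain almost nothing.
- **That the trial must show benefit separately in remission and in low disease activity.** Study design defines the two jointly as DAS28-CRP ≤ 3.2. With about 30 per arm in a stratum, the half-width would be 1.96 × √(0.4424/30), about 24 points, which is as large as the planned effect.

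**Conclusion.** The point holds as a worthwhile improvement to a valid analysis. That the required rise depends on V0 follows from the relapse definition by arithmetic and needs no assumption. That the primary comparison uses neither V0 DAS28-CRP nor gender is plain from the text.

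The benefit of adjusting is uncertain. It runs from none, if V0 values cluster between 2.6 and 3.2, to about 10 percentage points of power at 61 per arm, if V0 reaches down to 1.2 and later change varies little between patients. All of these sizes rest on assumed distributions. The first-crossing scenario, which follows the entry rule most closely, lies at the low end.

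**What to change.** Before database lock, prespecify the primary A vs C intention-to-treat analysis of relapse as adjusted for centre, gender and V0 DAS28-CRP. A logistic model reported as a standardised risk difference with its 95% CI would do.

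- Enter V0 in a form that allows the bend at 2.6, such as max(0.6, 3.2 − V0) or a spline. A single straight line in V0 misses it.
- Keep the centre-stratified Mantel-Haenszel estimate as a sensitivity analysis.
- Present any results for V0 < 2.6 and 2.6–3.2 as descriptive only.

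The model is feasible. With seven centres and the one-term form of V0 it has 1 + 6 + 1 + 1 = 9 coefficients besides the intercept. At 80 per arm and the planned rates it would have about 99 relapses (40 + 59) and 61 non-relapses. A rule for pooling very small centres would be sensible.

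The cost is analysis wording and slightly more analysis work, possibly for no gain in precision. No patient, visit, treatment or relapse definition changes.
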